In most treatment guidelines, cognitive-behavioral therapy (CBT) is regarded as the treatment-of-choice for BN [18]. Clinical targets in CBT include weakening the strength of core beliefs about low self-worth and compensatory beliefs about the need to control food intake, body weight and shape. Use of stimulus-control procedures to reduce the frequency of disordered eating, *ie.* bingeing and/or purging [19] is also central. Studies, systematic reviews and meta-analyses show promising effects of CBT for BED, and intermediate effects for BN, but the methodological quality of studies is low to moderate [20–22] even when often observed comorbid conditions are incorporated in the treatment [23–25]. New treatment approaches are called for because up to 50% of patients do not respond to CBT, even when the therapy is especially designed for ED [26].

Guided physical exercise (PE) may facilitate regulation of negative emotions [27], yet guided PE is rarely used in clinics [28] due to a fear of reinforcing the excessive exercise used to compensate for bingeing. A previous randomized controlled trial has shown that guided PE is as effective as CBT in alleviating BN symptoms [29]. The present study aims to replicate and expand on these findings.

Dietary therapy (DT) and counseling alone to correct the chaotic eating pattern has unclear empirical support [5, 30], but one review indicate some support to a possible *additive* effects of DT with CBT [31]. The present trial is the first one to examine the additive effects of DT and PE (PED-t) compared to CBT alone, and using a group therapy format.

Therapeutic alliance is an important moderator (or even mediator) of treatment effects in general; however, for EDs its impact is less understood [18, 32, 33]. High treatment expectations and installment of hope seems to predict treatment alliance in anorexia nervosa, but the relationship is uncertain for BN and BED [34]. Recent literature reviews have shown inconsistent findings across ED diagnoses, treatments, patient age groups and time (*eg*. early, mid or late) of assessment [31, 35, 36]. We hence included measures of alliance and group climate after every CBT and PED-t session to study the temporal order between these factors and response in both treatment arms [31].

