### Hypotheses and predictions

This trial will test six hypotheses:

1) Comparison of treatment arms: a) PED-t and CBT have comparable effects in terms of less symptoms of eating pathology, b) both perform better than a wait-list control group in reducing binge eating and/or purging, and c) both improve dietary intake.

2) Compared with CBT, the PED-t intervention produces a more rapid treatment response.

3) By improving physical strength and endurance, body composition, bone mass, and the nutritional and hormonal status, PED-t will surpass CBT in reducing the number and severity of medical complications.

4) Positive early changes in therapeutic alliance scores and group cohesiveness partly mediate effects of PED-t and CBT.

5) PED-t surpasses CBT in terms of a lower dropout rate and higher patient satisfaction with treatment.

6) The direct treatment costs are comparable for PED-t and CBT, but the indirect costs of PED-t are expected to be lower.

We predict that the PED-t combination will serve as an effective treatment method for BN and BED because the preoccupations of exercise and diets are transformed away from being ED-symptoms and toward functional coping and self-regulative activities. We also predict that the treatment effect of PED-t will be rapid and strong, defined according to a systematic review and meta-analysis [37], and the best empirically derived predictors of sustained remission at 6 and 12 months follow-up [38, 39] *ie*. as a 25% reduction in depression scores and ≤3 binge eating episodes a week during the first four weeks of treatment. Given that our novel treatment (PED-t) targets clinical features that occupy the sufferers’ minds, we expect a high level of treatment engagement, motivation and compliance. Such accomplishments may facilitate a stronger therapeutic alliance [40].

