## Methods and design

This randomized controlled trial includes three groups: participants are randomized to either the CBT or the PED-t treatment group, while participants having to wait represent the control group condition. After 16–20 weeks, these are randomized to either treatment arm. The treatments are delivered to groups consisting of 5–8 participants. It includes 20 therapy sessions stretching across 16 weeks. All outcome variables are measured five times: pre, post, 6, 12 and 24 months (Fig. 1). Mediator/moderator data (*ie*. therapy process variables) are collected after each treatment session, which yields excellent statistical power for conducting growth curve modeling, nuanced mediation or moderation analyses.

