### Statistical power and analyses

Analysis of covariance (ANCOVA) is used to raise statistical power. The effect size of the covariates is set to *R*
^*2*^ = 25%, alpha = .05 and 1-beta = .80. The CBT treatment effect for EDs using the Eating Disorder Examination Questionnaire is about *d* = 1.30 [45]. A small change (*d* = 0.30) in the wait-list condition requires 14 subjects in each group (total *N* = 28), but since the difference between the PED-t and CBT treatment conditions is of primary interest a non-inferiority margin of *d* = 0.45 is considered as clinically relevant [46]. This requires a sample size of 62 + 62 subjects, increasing to 72 + 72 when adjusting for the group therapy factor (intra-class correlation = .05, design factor 1.16). The longitudinal data will be analyzed using multilevel regression models to accommodate for dependency in the repeated data within subjects and within groups. The maximum likelihood procedure uses all information available, thus, handling dropout well. Multiple imputation will be used to impute missing values. Follow-up data is analyzed with mixed model regression to estimate correct between-group treatment effects adjusted for within-group variance components related to patients and groups. Moderator variables will be included to analyze whether any treatment effects are modified by variables as motivation, therapist alliance or group cohesiveness. If treatment arms do not differ in outcome, combined latent class growth curve modeling will be conducted to analyze reasons for individual differences at startup and in the rate of change across time.

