Patient satisfaction is measured using the “Expectations and experiences of ED-treatment” scale [78]. Qualitative approaches, such as in-depth interviews, may give additional insights into ED-patients’ perspectives and satisfaction with treatment [79, 80]. Therefore, a sufficient number of participants to meet data saturation criteria [81] are qualitatively interviewed about a) the immediate overall satisfaction with particular therapy sessions, the therapy process and outcomes, b) the recovery process; and c) the extent to which participants experience long-term treatment benefits. Interview data are analyzed in four steps within the framework of systematic text condensation [81]. Direct and indirect costs associated with treatment and follow-up are recorded prospectively.

Mediator variables comprise the “Working Alliance Inventory” [82] and the “Coerciveness” subscale from the “Therapeutic Factor Inventory” scale [83], both showing good psychometric qualities [84, 85].

Participants not continuing in the study will be compared to those who do continue by examining for differences in the pretest outcome measures.

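### Therapist alliance and group cohesiveness are planned as moderators although they are measured after treatment starts and are hypothesis 4's mediators, and the power claim for moderation is unsupported

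*Protocol article*

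**What the plan says.** The article gives the same two process variables different roles in different places.

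- Moderators, in Statistical power and analyses: "Moderator variables will be included to analyze whether any treatment effects are modified by variables as motivation, therapist alliance or group cohesiveness".
- Mediators, in hypothesis 4: "Positive early changes in therapeutic alliance scores and group cohesiveness partly mediate effects of PED-t and CBT". Measures and variables agrees. The sentence that opens "Mediator variables comprise the" goes on to list the Working Alliance Inventory and one subscale of the Therapeutic Factor Inventory. That subscale is printed as Coerciveness; I take it to be the cohesiveness measure.
- Left open, in Background: "Therapeutic alliance is an important moderator (or even mediator) of treatment effects in general". Methods and design likewise uses one joint label for mediator and moderator data.

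The timing is the same throughout. Background says: "We hence included measures of alliance and group climate after every CBT and PED-t session", with the aim "to study the temporal order between these factors and response in both treatment arms". Methods and design says of the mediator/moderator data that "therapy process variables) are collected after each treatment session", and adds of this collection: "which yields excellent statistical power for conducting growth curve modeling, nuanced mediation or moderation analyses". No calculation supports that last statement. The only sample-size figures, in Statistical power and analyses, are for the wait-list contrast and for PED-t against CBT.

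**The concern.** A moderator of a randomised treatment effect has to be fixed before allocation; otherwise the arms are not comparable within its levels. Alliance with a therapist and cohesion of a therapy group have no value before allocation. Once sessions start, both can respond to the treatment and to early improvement. An arm-by-alliance coefficient then mixes any real effect with differences between the arms in who forms a good alliance.

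The Discussion says the trial should help to show which patients respond best to which treatment. A spurious interaction would feed directly into that aim. The power statement adds to the risk, because it invites readers to take moderation results, positive or null, as well powered.

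**Working it through.** **1. Roles and timing.** The statistics section tests modification by alliance and cohesiveness. Hypothesis 4 and the measures section call them mediators. Background and Methods and design place their measurement after sessions. So the moderator sentence names two post-randomisation variables, and they are hypothesis 4's mediators. Motivation, the third variable named, is acceptable if it is measured at baseline.

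**2. Can the interaction be spurious?** A simulation with 72 women per arm, the planned number:

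- U = latent improvement or prognosis, standard normal.
- Outcome Y = 0.7·U + error. There is no treatment effect, no effect of alliance and no moderation.
- Alliance M = 0.3·arm + b(arm)·U + error.
- Model: Y on arm, M and arm × M, with the interaction tested two-sided at 5%.

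The coefficients 0.7, 0.3 and b are assumptions; the documents give none of them.

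| Coupling b, one arm v other | Errors of variance 1 | Y and M residuals scaled to unit variance |
|---|---|---|
| .4 v .4 | about 5% | about 5% |
| .5 v .2 | about 12% | about 26% |
| .6 v .2 | about 14% | about 41% |

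The excess over 5% comes entirely from unequal coupling, and its size depends on the scaling.

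**3. Reproducing the plan's sample size.** Inputs from Statistical power and analyses: margin 0.45 SD, alpha .05, power .80, design factor 1.16. With alpha taken as one-sided and no covariate reduction:

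n per arm = 2·(1.645 + 0.842)² / 0.45² = 61.1, so 62; 62 × 1.16 = 71.9, so 72.

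The stated 62 and 72 are reproduced. The planned 144 women are therefore worth 144 / 1.16 = 124 independent ones, or 62 per arm. These figures concern the main contrast only.

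**4. Power for moderation between arms.** For a baseline moderator splitting the sample in halves, there are four cells of N/4, so

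SE(interaction) = 4·√(1 − R²) / √N, with N = 124.

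- R² = 0: SE = 4 / 11.14 = 0.359.
- R² = .25, the plan's covariate figure: SE = 0.359 × √0.75 = 0.311.

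The documents give no interaction size. Taking 0.45 SD, as large as the margin, as an assumption, power = Φ(0.45/SE − 1.96):

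- R² = 0: Φ(1.253 − 1.96) = Φ(−0.707) = 24%.
- R² = .25: Φ(1.447 − 1.96) = Φ(−0.513) = 30%.

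The smallest interaction with 80% power is (1.96 + 0.842) × SE = 1.01 SD or 0.87 SD, about twice the margin.

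**5. Do session-level repeats help?** They add measurements, not women, so for this contrast they can only make the moderator more reliable. Take a continuous moderator with an interaction of 0.225 SD per SD, R² = .25, N = 124, and an assumed session-to-session correlation of .4 to .8. Power is 15–25% with one measurement and 29–30% with 20. Averaging the four post-baseline outcomes (assumed correlation .5 to .7) raises power for the 0.45 SD split-moderator interaction to about 38–45%.

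**The case against.** Three stronger readings are tempting, and the documents do not support them.

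- *Hypothesis 4 has no analysis.* A reader might infer this because the statistics section describes only a moderator model. But Methods and design announces mediation analyses, the measures section names the mediator instruments, and the Discussion speaks of searching for mediation effects and their timing. A condensed article may leave the mediation model to the full protocol or analysis plan.
- *The claimed power is absent altogether.* The power sentence covers growth curve, mediation and moderation analyses together. Dense repeats do help within-person growth and lagged models. What lacks support is the claim for moderation between arms.
- *The planned test will give false positives in up to two trials in five.* The upper figures need a large assumed difference in coupling and a particular scaling. Nothing in the documents establishes unequal coupling, and the article gives no model equation, so the simulated model is an illustration. It is still a fair one, since the arms differ in therapists and content.

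It can also be said that an arm-by-alliance term belongs in a standard mediation model. That is right. The difficulty is the interpretation in the statistics section, which is modification of the treatment effect. Finally, the point concerns secondary analyses and leaves the main comparison of PED-t with CBT untouched. That stands and limits its weight.

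**Conclusion.** The point holds, in two parts. First, the moderator label for alliance and cohesiveness conflicts with hypothesis 4 and the measures section. Because both are measured after treatment starts, an interaction with arm cannot be read as effect modification. How far this misleads depends on an unknown, the difference between the arms in how alliance follows improvement; the assumed cases run from no inflation to several times the nominal 5%.

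Second, the power statement is unsupported for moderation of outcomes between arms and is not met at the planned size unless the interaction approaches 0.9–1.0 SD. This rests on the plan's own effective sample, a two-sided 5% test and an evenly split moderator. It should be corrected, but it does not affect the primary comparison.

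**What to change.** - In Statistical power and analyses, limit moderators to variables measured before randomisation, for example baseline motivation or treatment expectations.
- Analyse alliance and cohesiveness only as mediators under hypothesis 4: early-session scores predicting later outcome, adjusted for baseline symptoms, and for interim symptoms where these are collected. The text shown lists outcomes at five times from pre-treatment to 24 months, and the schedule figure is missing, so symptom data between sessions cannot be assumed.
- Allow an arm-by-mediator term inside that model, but do not report it as moderation. Mediation estimates also lack the protection of randomisation, which is why the symptom adjustment is needed.
- In Methods and design, restrict the power claim to within-person growth models and label between-arm moderation exploratory.

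These are changes of wording and analysis and need no new patients or measurements. The price is that moderation claims for alliance and cohesiveness are given up.

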### Interventions

#### The physical exercise and the dietary therapy (PED-t)

##### Physical exercise

The PED-t is a treatment method particularly designed for BN and BED by our research group, and adheres to recent guidelines developed from systematic reviews to successfully use therapist guided physical exercise [47], and recommendations for a minimal training volume to accomplish a health benefit [48–51].

The intervention aims to (re)establish healthy eating and exercise routines, to change body ideals by focusing on the body’s functionality rather than body appearance and to provide knowledge about the harmful metabolic effects of swings between dieting and food craving. Education about harmful effects of unhealthy behavior is given and how basic and sports related nutritional needs may be balanced.

Three physical trainers and three dieticians conduct the intervention, all holding a master degree in sport sciences and having about three years of practice with supervised exercise. To qualify as a PED-t therapist the physical trainers hold a bachelor’s degree in physical exercise and health or exercise medicine.

The weekly training program in PED-t aims to establish a healthy volume of physical activities, emphasizing the training principles of progression and variation. The exercise program consists of three weekly exercise sessions, each of 40–60 min’ duration. Two sessions are resistance exercise of which one is supervised. The third exercise session consists of unsupervised pyramid interval running, involving shifts between intensive work-periods and active rest-periods with progressive duration (from one minute work period to 4 min of work period).

There are three reasons to focus on giving the participants experience with resistance exercise. First, regular resistance exercise may improve metabolism and bone mineral density, and increase muscular mass and strength [49, 52–54]. Change in body composition further increases the potential for improvement in energy metabolism, weight control and metabolic status [52, 55]. Second, the repeated bouts of supervised resistance exercise, involving technical guiding/corrections while lifting may improve body posture and awareness. Third, strength training involves easily coordinated movements, which may increase the likelihood of positive experience of mastery and weekly progression in performance. These bodily experiences during and after a period with exercise training, have potential to improve body image, self-perception, affect regulation and feeling of coping [56–60]. Intensive work periods, followed by active recovery periods, as practiced with interval training may improve cardiovascular health more effectively and with a lower risk compared to the extended exercise regimen often seen in ED [49, 61–64].

The physical strength-training program intends to improve maximal strength and growth. It is divided into five microcycles with both linear and daily variation in training load [65]. Linear progression involves increased intensity and reduction of training volume over a period of time, with the objective to increase maximal strength. Each week consists of one supervised heavy load, and one unsupervised medium load session. In the former, the number of repetition maximum (RM) increases progressively during the 16 weeks, while in the medium load session, relative load is kept constant at 10RM.

The exercises in the resistance exercise program are squats in smith-machine, lunges with dumbbells, seated dumbbell shoulder press, bench press, latissimus pulldown and seated row in cable machine. The intensity and work periods in the interval running program, follows a traditional pyramid structure performed with progressive interval periods and active rest periods, and then repeated in reverse. After a 10 min warm up, the interval periods are initiated by the first work period of 1 min and a 30 s active rest period (lower intensity), followed by the next work periods of 2 and 3 min and their corresponding rest periods of 60 and 90 s respectively. During the last six weeks, an extra interval period adds to the program with 4 min of work and 2 min of active rest (Table 1).

**Table 1 Tab1:** Overview of the exercise module of the PED-t treatment arm

		SUPERVISED EXERCISE	UNSUPERVISED EXERCISE	
Week	Microcycle	Resistance exercise	Interval running	Resistance exercise
1–3	1	10 RM	Pyramid interval	10 RM
4–7	2	8 RM	Pyramid interval	10 RM
8–11	3	6 RM	Pyramid interval	10 RM
12–14	4	4 RM	Pyramid interval	10 RM
15–16	5	2 RM	Pyramid interval	10 RM

Resistance load is given as number of repetition maximum (RM)

During the mid-period (week 8–11) a supervised fourth, weekly group exercise session is introduced, leading the participants to do both the resistance exercise sessions unsupervised. The intention of introducing the participants to the fourth, additional exercise sessions is to inspire them to find a variety of training modalities that can improve physical fitness and promote training joy. Further, the intention with the group sessions is also to make them more experienced in exercising together with others, supervised by an instructor. The four sessions are Total body Resistance eXercise (TRX), suspension training or Cat slide exercise, one boot camp session, one indoor cycling class, and one combat inspired session.

##### Dietary therapy

The dietary therapy consists of three modules (Table 2), aiming to re-establish healthy dietary routines through weekly lectures, and on discussions related to the weekly topics and the experiences by the participants. Between every session, the participants register the meals they are consuming (pen and paper), and work on individual tasks related to dietary routines (increase number of meals per day, increase volume of food in each meal, improve the composition of the meal etc.).

**Table 2 Tab2:** Overview of the content of the dietary module of the PED-t treatment arm

Module	Therapy session	Targets	Main content
1	1–5	Dietary routines & structure	Meal frequency
			Portion size
			Eating situation
			Exercise theory
			Repetition and summary
2	6–17	Nutritional knowledge & practical skills	Energy needs
			Daily routines
			Nutrients
			Nutritional labels
			Impulsive food shopping
			Exercise theory
			Sports nutrition
			Repetition and summary
3	18–20	Summary of future plans	Reflections, repetition and summary
			Presenting a personal plan for the future (exercise, diet, daily routines)

#### The cognitive behavioral therapy (CBT)

Our manual-based CBT has a group format, and rests on the transdiagnostic model of generic core ED-pathology across ED-diagnoses [45]. The treatment runs through four stages (Table 3). All sessions are videotaped and coded according to a CBT manual adherence form [66]. Psychologists who are experienced with CBT and EDs run the CBT treatment.

**Table 3 Tab3:** Overview of the cognitive behavior therapy (CBT) module

Stages	Therapy session	Targets	Main content
1	1–4	Engagement, preparation and early behavior change	Educate about the nature of CBT and how the therapist and the participants work together
			Engage the participants in the treatment.
			Develop a case formulation for each participant.
			Strategies to take control over the behavioral symptoms of BN and BED
2	5–6	Monitoring and evaluating progress and barriers to change	A detailed review of progress so far, and to identify barriers to change
3	7–16	Modifying the core pathology of ED	Reduce the over-evaluation of weight and shape
			Address extreme dieting, binge eating, and purging
4	17–20	Consolidating change and relapse prevention	Secure that progress is maintained after treatment end

